## Abstract

**Background:**

Siblings and parents of children with neurodevelopmental disorders are at risk of mental health problems and poorer family communication. Some group interventions for siblings exist, but few have clearly described parent components and none are considered evidence-based.

**Methods:**

We are conducting a randomized controlled trial comparing a five-session manual-based group intervention for siblings (aged 8 to 16 years) and parents of children with neurodevelopmental disorders to a 12-week waitlist, called SIBS-RCT. The intervention comprises three separate sibling and parent group sessions and two joint sessions in which each sibling talks to their parent alone. The intervention aims at improving parent-child communication and covers themes such as siblings’ understanding of the neurodevelopmental disorder, siblings’ emotions, and perceived family challenges. Participants are recruited through municipal and specialist health centers across Norway. The primary outcome is sibling mental health. Quality of life and family communication are secondary outcomes. Participants are block-randomized to the intervention or 12-week waitlist in groups of six. Measures are collected electronically at pre- and post-intervention/waitlist, as well as 3, 6, and 12 months post-intervention. The main effect to be examined is the difference between the intervention and waitlist at 12 weeks post. All outcomes will also be examined using growth curve analyses. We plan to include 288 siblings and their parents by the end of 2022.

**Discussion:**

SIBS-RCT represents a major contribution to the research and practice field towards establishing an evidence-based intervention for siblings. In the event that intervention and waitlist are no different, the impact of SIBS-RCT is still substantial in that we will aim to identify participant subgroups that show positive response and effective components of the SIBS manual by examining group leader adherence as an outcome predictor. This will allow us to continue to re-engineer the SIBS manual iteratively to improve outcomes, and avoid the promotion of a less-than-optimal intervention.

**Trial registration:**

ClinicalTrials.gov NCT04056884*.* Registered in August 2019

## Administrative information

The order of the items has been modified to group similar items (see http://www.equator-network.org/reporting-guidelines/spirit-2013-statement-defining-standard-protocol-items-for-clinical-trials/).

## Introduction

### Background and rationale {6a}

Sibling relationships, our longest lasting bonds, represent a unique source of learning, support, and rivalry. Chronic illness in children involves risk for reduced well-being among siblings [1]. The mechanisms behind this risk are associated with (1) the chronic illness itself (e.g., behavior problems), (2) siblings’ lack of illness knowledge (e.g., misunderstandings), (3) poor parental mental health due to extra care responsibilities, and (4) poor family communication (e.g., less open and warm communication [2–4]).

Previous sibling interventions have shown positive outcomes for siblings’ well-being (e.g., [5, 6]). However, systematic reviews have demonstrated that no intervention has an established evidence-base [7, 8]. Therefore, we plan to examine a group intervention for siblings and parents of children with chronic illness in a randomized controlled trial (SIBS-RCT). SIBS-RCT is based on preliminary studies conducted by our consortium. First, we conducted a qualitative study of group sessions for 58 siblings of children with rare disorders. We found that siblings have limited disorder knowledge [4], conflictual emotions and passive coping strategies [9], and unique perspectives on their brothers and sisters with disorders [10]. Based on user feedback and these preliminary findings, we developed the SIBS intervention, a 5-session manual-based program with parallel sibling and parent groups. A unique feature of the SIBS intervention is integrated sibling-parent dialogs, which we added due to evidence of poor family communication in families of children with chronic illness [2].

We examined the SIBS intervention in an open trial with 107 families of children with rare disorders, autism, congenital heart disease, cerebral palsy, or Down syndrome. We found significantly improved sibling mental health and family communication from pre-intervention to 6-month follow-up (mean effect size *d* = 0.43) [11]. Acceptability and feasibility were promising, with a 54% response rate, 86% group leader manual fidelity, and mean sibling and parent satisfaction scores of 3.6 on a 1–4 rating scale.

Examining the effects of the SIBS intervention in an RCT design, as proposed herein, is the next critical step to establish it as an evidence-based intervention for siblings. We focus on neurodevelopmental disorders (ND), defined by impaired development of the central nervous system, affecting behavior, physical abilities, and mental health [12]. We decided on ND for three main reasons. First, ND represent a large group of physical and mental health conditions (e.g., autism spectrum disorders, cerebral palsy, epilepsy, intellectual disability), which enables our results to be generalized across conditions. Second, evidence suggests the impact of chronic illness on siblings is transdiagnostic and not disorder-specific [7]. Therefore, including across the ND spectrum is reasonable in comparison with focusing on specific ND diagnoses only. Third, the impact of ND represents a major public health challenge, as up to 15% of children have ND, and many of these have at least one typically developing sibling [12]. We present important advances of the current SIBS-RCT relative to past trials in Table 1.

**Table 1 Tab1:** Methodological advances of current SIBS trial relative to past sibling intervention trials

Documented limitations^a^	SIBS study features
Few controlled trials^b^	Randomized controlled design
Small sample sizes/insufficient power	A sample of 288 siblings based on power analysis
Unclear inclusion criteria	Child with ND enrolled in health services is the main inclusion criteria
Lack of standardized measures	Well-validated measures
Single raters only (most often parents)	Multi-informant (siblings, parents, teachers, clinicians, observers)
Cross-sectional/lack of follow-up data	Prospective with multiple assessment points up to 12 months post
No session description/protocol/manual	Detailed session-by-session manual
Unclear description of parent involvement	Parallel and joint parent component
No adherence data	Group leader adherence and competence measured

^a^Based on reviews ([7] 17 studies and [8] 16 studies)

^b^One randomized controlled trial has been conducted (*N* = 21) [5]

### Objectives {7}

Objective 1 is to promote sibling well-being by addressing research question 1: *Does the SIBS intervention improve mental health for siblings of children with ND compared to waitlist?* and research question 2: *What are the long-term trajectories of sibling well-being, in terms of mental health, family communication, quality of life, sibling adaptation, and disorder knowledge from pre-intervention to 12-month follow-up?* Based on the findings from our open trial, we hypothesize that the SIBS intervention will outperform waitlist and that the mean 12-month trajectories will indicate significantly improved well-being. Objective 2 is to identify those siblings who are most likely to benefit from the SIBS intervention by addressing research question 3: *Which factors (i.e., ND impairment, parent mental health, family stress) predict outcomes of the SIBS intervention?* Previous findings indicate higher ND impairment and poorer parent mental health will be associated with poorer sibling mental health [1, 3]. However, there is limited knowledge upon which to base hypotheses about predictors of effects. The third research question is therefore exploratory. SIBS-RCT represents a major contribution to the research and practice field towards establishing an evidence-based intervention for siblings. In the event that intervention and waitlist are no different, the impact of SIBS-RCT is still substantial in that we will aim to identify (a) participant subgroups that show positive response and (b) effective components of the SIBS manual, by examining group leader adherence as an outcome predictor. This will allow us to continue to re-engineer SIBS-RCT iteratively to improve outcomes, and avoid promotion of a less-than-optimal intervention.

### Trial design {8}

SIBS-RCT is a randomized controlled trial comparing a 5-session group intervention for siblings and parents of children with ND to a 12-week waitlist comparator control. We decided on a 12-week waitlist as this is the longest permitted wait for intervention for internalizing and externalizing problems in the Norwegian public mental health system. For this reason, and because some participants may have high clinical symptom levels, a longer waitlist would be unethical.

## Methods: participants, interventions, and outcomes

### Study setting {9}

SIBS-RCT is conducted across ten sites covering urban and rural areas in Norway (see Fig. 3). We include specialist and municipal health services as both tiers provide services to children with ND, and both are required by legislation to address siblings’ needs. All sites volunteer to SIBS-RCT. A full list of sites can be obtained by contacting the first author.

### Eligibility criteria {10}

The inclusion criteria are as follows: (1) being the sibling of a child diagnosed with ND who is aged 0 to 18 years and who receives specialist and/or municipal health services. The service-recipient criterion has been set to ensure ND impairment is in the clinical range, as ND impairment is a consistent predictor of sibling well-being [1]; (2) sibling age 8–16 years, to ensure generalizability across age spans. This age range was used in our open trial [11]. Sibling groups will be age-clustered to ensure a maximum 4-year age span from the youngest to the oldest participant; and (3) one parent able to attend the intervention. Families choose which parent. We applied this in our open trial due to the care needs of the child with disorder, with two thirds of participating parents being the mother (34% fathers). We collect data from both parents regardless of participation and encourage the participating parent to discuss the intervention with the non-participating parent. The follow-up questionnaire addresses the involvement of the non-participating parent, and we control for participating parent in all analyses of outcomes. If more than one sibling from the same family attends, both parents can participate.

The exclusion criteria for siblings are as follows: (1) being enrolled as primary patients in specialist health services and (2) ND diagnosis. Eligibility criteria for group leaders are as follows (1) employment in municipal or specialist health services, (2) trained as a health professional (e.g., nurse, social worker, special educator, psychologist); and (3) completion of a training package comprising a 5-session e-learning course (which takes about 1 h to complete) and a 2-day practical workshop. Throughout the data collection period, we invite all group leaders to supervision webinars 2–3 times per year. We also arrange regular site visits where practical matters and questions about the intervention are discussed.

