#### Intervention description {11a}

The intervention comprises 5 sessions delivered over 2 days, 1 week apart. Day 1 comprises sessions 1–3 (3.0 h including breaks). Day 2 comprises sessions 4–5 (2.5 h including breaks). Sessions 1, 2, and 4 are parallel (separate) group sessions for siblings and parents. Sessions 3 and 5 are integrated sibling-parent dialogs in which each sibling and parent talk together, separate from other participants. Two main themes, both empirically derived sibling challenges, provide the basic components of the intervention: disorder knowledge and emotional experiences. These themes are discussed in relation to the overarching component, family communication. Session 1 is the introduction. Sessions 2–3 focus on siblings’ ND knowledge. Sessions 4–5 focus on siblings’ emotional experiences based on cognitive-behavioral principles about how thoughts and behaviors influence emotions. In sessions 2 and 4, siblings generate lists of ND questions and challenges, respectively, which a group leader then brings to the parent group for discussion. In sessions 3 and 5, each sibling discusses their questions and challenges with their parent. The parent sessions focus on communication training focused on ND knowledge and siblings’ emotional challenges, introducing the SIBS motto “listen, explore, validate,” using standardized video examples of real sibling-parent dialogs with various degrees of open-exploratory communication as a basis for discussion. Parent sessions also comprise psychoeducation about sibling challenges and introduction to cognitive-behavioral principles about emotional coping. The SIBS intervention is outlined in a step-by-step manual for group leaders (see Fig. 1).

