### Assignment of interventions: allocation

#### Sequence generation {16a}

Participants are randomly assigned to either intervention or 12-week waitlist (1:1), in clusters of 6, stratified by participant age to avoid > 4-year age gaps between participants in the intervention groups. Each site requests a randomization number when the site has ~ 6 consenting participants within each age range. A pre-generated randomization indicates whether the cluster will be either intervention or waitlist. The allocation sequence was computer-generated by a research coordinator who is independent of the PI. The sites and participants are advised of their allocation approximately 2 weeks prior to group dates, to respect their time management needs (e.g., planning time off school and work for participants; allowing time for other clients for group leaders). Participants allocated to waitlist receive the intervention after 12 weeks. The dates for the potential waitlist groups are included in the original invitation letter to ease families’ planning.

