### Statistical methods

#### Statistical methods for primary and secondary outcomes {20a}

The main effect is measured as the difference between the intervention group and the waitlist group in SDQ scores from pre-intervention to 3 months, reported by siblings, parents, and teachers. This is investigated using mixed ANOVA, and effect sizes will be reported as Cohen’s *d*. To examine the effects beyond waitlist for the complete sample, we apply growth curve modeling, which enables us to investigate both mean changes at a group level over time and individual growth trajectories, with the inclusion of individuals with partial/missing data [26]. A series of linear mixed models are fitted. A model with only fixed and random intercepts serves as the null model, to which subsequent unconditional models of time will be compared. Finally, group membership and control variables are included in a set of conditional models, through which the longitudinal effect of the intervention is investigated. Growth curve models are fitted separately for the intent-to-treat sample and per-protocol, excluding participants with concomitant sibling care during follow-up. Multilevel analyses controlling for nesting (group and site level) are conducted with MPlus. Other analyses are conducted using updated versions of IBM SPSS and R.

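### Enrolled siblings of one family more than 4 years apart can be randomised to opposite arms and are not linked in the analysis; the effect is probably small and cheap to guard against.

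*Protocol article*

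**What the plan says.** Eligibility criteria {10} foresees several siblings from one family: "If more than one sibling from the same family attends, both parents can participate". The same section sets the age range, "sibling age 8–16 years, to ensure generalizability across age spans", and the limit within a group: "Sibling groups will be age-clustered to ensure a maximum 4-year age span from the youngest to the oldest participant".

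Sequence generation {16a} states the unit of allocation: "Participants are randomly assigned to either intervention or 12-week waitlist (1:1), in clusters of 6, stratified by participant age", and "A pre-generated randomization indicates whether the cluster will be either intervention or waitlist". Implementation {16c} gives each group its own number from a pre-generated list. No section says how a second sibling from an already enrolled family is allocated.

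Intervention description {11a} shows that parents are treated directly: "The parent sessions focus on communication training focused on ND knowledge and siblings’ emotional challenges". Under Outcomes {12}, parents also rate the sibling on the primary measure, the SDQ.

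For the main effect, Statistical methods {20a} says "This is investigated using mixed ANOVA". For clustering it says "Multilevel analyses controlling for nesting (group and site level) are conducted with MPlus". Sample size {14} plans 288 siblings but starts from 136 families. Implementation {16c} gives the target as 288 families.

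**The concern.** Two enrolled siblings more than 4 years apart cannot share a group, so each has a separate allocation. If they draw opposite arms, the parent trained with one child goes home to the waitlisted child and also rates that child, unmasked. Any benefit passed on in this way before the waitlist reassessment makes the arms more alike and pulls the estimated effect toward zero.

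There is also a modelling gap. Siblings share a home and raters. A group effect captures some of this when they attend together, but it cannot connect children in two groups. Finally, 288 siblings and 288 families are the same number only with one sibling per family, which the eligibility section does not require.

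**Working it through.** **1. Can siblings be split?** Ages 8–16 allow a gap of up to 16 − 8 = 8 years, against a limit of 4 within a group. Pairs with a larger gap must be in different groups. With independent 1:1 draws, such a pair falls in opposite arms about half the time. It is slightly more often for neighbouring list numbers, because Implementation {16c} allows no more than 3 consecutive allocations to one arm.

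**2. When would exposure occur?** Under Implementation {16c}, waitlist families are reassessed 2 weeks before an intervention date that lies about 12 weeks after the initial group date, so at about week 10. Exposure before that point requires the sibling's intervention group to have run by then. Each site requests a number when an age range has filled, so two age groups may run together or months apart.

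**3. The plan's own sample size (Sample size {14}).**
- Inflation factor: 1 + (6 − 1) × 0.11 = 1.55, as stated.
- 136 × 1.55 = 210.8, stated as 211.
- 211 / (1 − 0.27) = 289, stated as 288; conversely 288 × 0.73 = 210.2.

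These steps reproduce. The only clustering they allow for is one ICC applied at group size 6.

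**4. Dilution.** The documents do not give the share of siblings with an enrolled brother or sister in another group. I assume 5–20%. Half of these pairs in opposite arms gives f = 2.5–10% of waitlist siblings exposed. Let c be the share of the effect carried over, assumed to be 50–100%.

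Diluted effect = 0.4 × (1 − f × c). Power, rescaled from the stated 80% at 0.4 and taking the 5% level as two-sided (the article does not say), = Φ[(1.960 + 0.842) × (1 − f × c) − 1.960].

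| f | c | Effect | Power |
|---|---|---|---|
| 0.025 | 0.5 | 0.4 × 0.9875 = 0.395 | Φ(0.807) = 0.79 |
| 0.10 | 0.5 | 0.4 × 0.95 = 0.38 | Φ(0.702) = 0.76 |
| 0.10 | 1.0 | 0.4 × 0.90 = 0.36 | Φ(0.561) = 0.71 |

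The last row assumes that a child who attended nothing gains the whole effect, and every row assumes that all opposite-arm pairs overlap in time. The table is therefore an upper bound for the assumed shares.

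**5. Standard error.** Let N = 288, S and O be the numbers of same-arm and opposite-arm pairs, and ρ the within-family correlation beyond what the group level absorbs. With the group design effect of 1.55:

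true SE / SE ignoring family = √[1 + 2ρ(S − O) / (288 × 1.55)], with 288 × 1.55 = 446.4.

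Neither the share of paired siblings nor ρ is given. I assume 10–30% of siblings in pairs (14.4 to 43.2 pairs) and ρ of 0.2–0.5.
- All pairs in the same arm: √(1 + 5.76/446.4) = 1.006 up to √(1 + 43.2/446.4) = 1.047. The reported SE is too small.
- All pairs in opposite arms: √(1 − 5.76/446.4) = 0.994 down to √(1 − 43.2/446.4) = 0.950. The reported SE is too large.
- Half and half: 1.00.

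**6. Unit.** If 10–30% of 288 siblings come in pairs, the number of families is 288 × 0.95 = 274 down to 288 × 0.85 = 245, not 288.

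**The case against.** The strongest reply is that the sentence on both parents fits siblings who attend together. In sessions 3 and 5 each sibling talks alone with a parent, so two siblings in one group need two parents, whereas siblings in different groups could bring the same parent each time. Implementation {16c} also counts groups in families. This stands: the sentence shows that multi-sibling families are admitted, not that they are expected to be split. It cannot help a pair more than 4 years apart, but no document says how many such pairs there will be.

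Second, a condensed article may leave the allocation of a second sibling to the full protocol. That is fair, so the missing rule is not the finding by itself. The point rests on what is stated: the age limit, allocation by group, two named nesting levels, and one number serving for both siblings and families. The adjustment for participating parent in {10} concerns which parent attends; it is not described as a family term.

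A reader might go further and infer that waitlisted siblings do receive part of the intervention, or that the planned standard errors are too small. The documents support neither. Exposure depends on timing that is not fixed, and the intervention includes sibling sessions and dialogs that the waitlisted child has not had. For the very pairs in question, those in opposite arms, ignoring a positive family correlation makes the standard error too large.

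It is also tempting to say that every later sibling should take the first sibling's arm. That would either dictate the arm for the other families in the later group or place a child in a group whose arm is already known, against the concealment described in {16b}.

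**Conclusion.** The point holds in a limited form. Under the stated rules, enrolled siblings more than 4 years apart must be in separately randomised groups, can be in opposite arms, and are not linked by the group-and-site nesting. The article also equates 288 siblings with 288 families, although its eligibility rule does not make them equal.

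The size is unknown and probably small. With 2.5–10% of waitlist siblings exposed and 50–100% carry-over, power drops from 80% to 79–71%; realistic values lie toward the upper figure, because full carry-over and complete overlap in time are unlikely. The standard-error error is about 1–5% under the assumed ranges, has no fixed direction, and is roughly nil if half the pairs are in opposite arms. All these figures rest on shares, carry-over and correlations that I assumed. Only the mismatch of units stands regardless of them. This is an inexpensive improvement to the plan, not a threat to the trial's validity.

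**What to change.** 1. **Sequence generation {16a} and Implementation {16c}:** name one index sibling per family before allocation, and use only index siblings in the primary analysis. Where two groups that share a family are ready at the same time, they may be randomised as a linked pair with one concealed draw. No group or child should be given an arm that is already known.
2. **Statistical methods {20a}:** in any analysis that includes all siblings, add a family random effect or family-clustered standard errors. Add a sensitivity analysis that excludes families split across arms. The index rule alone removes dependence but not exposure, since a waitlisted index child may still have a brother or sister in the intervention arm.
3. **Sample size {14} and Implementation {16c}:** state whether 288 counts siblings or families, and use that unit throughout.

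The cost is that a few second siblings leave the primary analysis, and linked groups give slightly fewer independent draws. The allocation part helps only groups not yet randomised. The analysis part should be fixed before outcome data are analysed.
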